#### Secondary outcome measures.

Intraoperative ventilation settings will be evaluated. Additionally, the incidence of unplanned postoperative ventilation, oxygen therapy, ARDS, respiratory insufficiency, pneumonia, pulmonary embolism, pneumothorax, myocardial infarction, myocardial damage, cardiac death, cardiac arrhythmias, atrial fibrillation, stroke, acute renal failure and other serious postoperative complications are going to be analyzed.

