Postoperative parameters	PaO_2_, PaCO_2_, FiO_2_, pH value, respiratory rate, blood pressure, heart rate, temperature, SpO_2_, hemoglobin
Postoperative care	admission to the intensive care unit, reason for admission to the intensive care unit, occurrence of nausea and vomiting, pain intensity, need for oxygen therapy or mechanical ventilation, reason for oxygen therapy and mechanical ventilation, complications during the first 5 postoperative days
Postoperative pain therapy	opioids, peripheral analgesics, regional analgesics, other
Postoperative delirium screening	on postoperative days 1–5 using 3DCAM, 4AT and CAM-ICU in the intensive care unit

The occurrence of postoperative delirium is assessed during daily rounds by trained staff in the first five days after the operation, in accordance with the European guideline. The 3DCAM test and 4AT are used for this purpose.

Additionally, the CAM-ICU (Confusion Assessment Method for the Intensive Care Unit) is routinely used by medical staff in the intensive care unit. All three instruments are validated and reliable screening methods for detecting delirium [14,15].

Withdrawal from the study happens may occur after the patient revokes consent, the planned operation is canceled, or if the study protocol is violated. All study participants are visited on all five postoperative days. To determine the incidence of delirium and other complications, such as cardiac and pulmonary, only patients who have spent at least one night on a surgical ward after surgery and who have undergone at least one postoperative screening will be included. Patients who do not complete these criteria are excluded from the statistical analysis. This methodological approach ensures a careful and representative analysis of postoperative events.

A recruitment period of approximately 16 months is planned to include 266 patients. A dropout rate of 10% of the recruited patients will be tolerated. If the dropout rate exceeds this threshold, further recruitment will be undertaken. The conduct of this study was guided by the recommendations of the STROBE checklist (Strengthening the Reporting of Observational Studies in Epidemiology) to ensure transparency and scientific rigor. All relevant points of the checklist were considered in the planning and conduct of the study to maximize the quality and reproducibility of the results.

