### Termination criteria

Consent to participate in the study may be withdrawn at any time, without providing reasons and without negative impact on further medical treatment. In the event of withdrawal from the study, all personal data already collected will be deleted immediately and completely.

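### The analysis set requires a surgical-ward night and a screening after surgery, so it drops patients who die or stay in the ICU without reaching a ward, along with their events

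*Protocol article*

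**What the plan says.** All places are in the protocol article.

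- **Study design, scope of the rule.** It is introduced with "To determine the incidence of delirium and other complications, such as cardiac and pulmonary", so it governs the primary outcome and the complications alike.
- **Study design, content of the rule.** Those analysed are "only patients who have spent at least one night on a surgical ward after surgery and who have undergone at least one postoperative screening". For the rest: "Patients who do not complete these criteria are excluded from the statistical analysis". The reason given is "This methodological approach ensures a careful and representative analysis of postoperative events".
- **Study design, ICU assessment.** Besides 3DCAM and 4AT, "the CAM-ICU (Confusion Assessment Method for the Intensive Care Unit) is routinely used by medical staff in the intensive care unit". Table 2 lists CAM-ICU under postoperative delirium screening for days 1 to 5.
- **Primary outcome measures.** A positive result on any one of the instruments in use meets the endpoint.
- **Secondary outcome measures.** The list includes unplanned postoperative ventilation, ARDS, stroke and "myocardial infarction, myocardial damage, cardiac death".
- **Study design, data sources.** Anesthesia and surgery data come from hospital records. Intraoperative complications, ICU admission, postoperative ventilation and day-of-surgery complications are all documented.

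**The concern.** An analysis set should rest on facts fixed before the outcome can occur, or at least on facts unrelated to it. Here both conditions are consequences of the postoperative course. A patient who never reaches a surgical ward leaves numerator and denominator together, and such patients include those with the most severe courses.

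The rule also works against the article's own endpoints. A patient with a positive CAM-ICU who dies in the ICU has met the primary endpoint and is still not analysed. A death in theatre from a cardiac cause is a listed secondary outcome that this set cannot contain. For events read from the records, a delirium screen is not needed to establish them.

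The study asks whether prior infection raises perioperative complications. If it does, exclusion may differ between the groups, and the comparison is then made between two differently selected sets of patients.

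**Working it through.** **1. Who is kept and who is dropped, reading the rule literally**

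| Postoperative course | Ward night | In the analysis? |
|---|---|---|
| Ward, screened at least once | yes | yes |
| ICU, CAM-ICU positive, later a ward night | yes (no time limit is stated) | yes |
| ICU, CAM-ICU positive, dies in ICU | no | no, although the primary endpoint is met |
| ICU, then transferred without a surgical-ward night | no | no, whatever events occurred |
| Dies in theatre | no | no, although cardiac death is a listed outcome |
| Ward night, never screened | yes | no, although complications are in the records |
| Discharged on the day of surgery | no | no |

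Rows three to five are the conflict with the two outcome sections and with the claim of representativeness. The last row shows that low-risk patients can be dropped too.

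**2. The plan's own figures**

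The article plans 121 per group, 242 in total, raised by 10%: 242 × 1.10 = 266.2, which reproduces the stated 266. It tolerates a dropout rate of 10%. It does not say whether patients who fail the rule count as dropouts, and it gives no exclusion rate and no delirium rate. Every rate below is therefore an assumption.

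**3. Effect on delirium incidence**

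Let p be the true incidence, e the share excluded and q the incidence among those excluded. The incidence observed under the rule is (p − e·q)/(1 − e). With p = 20%:

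| e | q = 0% | q = 5% | q = 50% | q = 80% |
|---|---|---|---|---|
| 5% | 21.1% | 20.8% | 18.4% | 16.8% |
| 10% | 22.2% | 21.7% | 16.7% | 13.3% |

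Example: (0.20 − 0.05 × 0.80)/0.95 = 0.168. The observed figure falls if those excluded are mainly high-risk and rises if they are mainly same-day discharges.

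**4. Effect on the comparison**

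Take true rates of 15% (no prior infection) and 30% (prior infection), with q = 80% in both groups. The true odds ratio is (0.30/0.70)/(0.15/0.85) = 2.43. Power with 121 analysed per group (two-sided 5%, normal approximation) is 80%.

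- Exclusion of 2% and 8%: (0.15 − 0.016)/0.98 = 13.7% and (0.30 − 0.064)/0.92 = 25.7%. Odds ratio 2.18, power 65%.
- Exclusion of 5% in both: (0.15 − 0.04)/0.95 = 11.6% and (0.30 − 0.04)/0.95 = 27.4%. Odds ratio 2.88, power 88%.
- No true difference (20% in both), exclusion of 2% and 8%: (0.20 − 0.016)/0.98 = 18.8% and (0.20 − 0.064)/0.92 = 14.8%. Prior infection would look protective by 4 points.

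The bias can go towards no effect, away from it, or past it.

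**5. Effect on a severe event**

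If an event has a true incidence of 5%, half of those affected never meet the rule and nobody else is excluded, the observed incidence is 0.025/(1 − 0.025) = 2.6%. For death in theatre, or in the ICU before any ward night, the loss is complete whatever rates are assumed.

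**The case against.** The case on the other side has real weight.

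- **ICU patients are not shut out as a class.** The ward night has no time limit and CAM-ICU can serve as the screening, so an ICU patient who later spends one night on a surgical ward is analysed. This stands: the conflict is confined to patients who never reach a ward. A reader might infer that the severe secondary outcomes are largely eliminated. The documents do not show that, because survivors who reach a ward and are screened count for all of them.
- **The direction is open.** A reader might infer that delirium is bound to be undercounted and the association pulled towards no effect. Neither follows. Same-day discharges are dropped as well, and equal exclusion can raise the odds ratio, as shown above.
- **No exclusion rates are given,** and the patients are elective and able to consent, so few may fail the rule. This stands as a limit on size, but it does not justify the rule.
- **One common set is a simplification.** It would be acceptable if membership did not depend on the outcomes under study. Here it does. Nor is the matter left to an analysis plan, because the article itself fixes the set.

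A further inference is tempting: that withdrawal "or if the study protocol is violated", together with the sentence that "all personal data already collected will be deleted immediately and completely", removes agitated patients who refuse screening and erases their data. The text does not support this. Violation is undefined and not tied to the postoperative course, withdrawal is only something that may occur, and the deletion sentence directly follows one on revoked consent and is most naturally read as referring to it. It forms no part of this point.

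**Conclusion.** The rule is wrong as written. It selects patients on their postoperative course, applies that selection to the primary and the secondary outcomes, and contradicts both the any-instrument endpoint with CAM-ICU and the listing of fatal and ICU-bound events. It does not deliver the representative analysis claimed for it.

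What is certain is narrow: events in patients who die or leave hospital care at this site without a surgical-ward night are lost. What is uncertain is the net effect on delirium incidence and on the group comparison. The illustrations show that exclusions of 2% to 8% can matter (power 80% to 65%, or a spurious 4-point difference), but they assume 80% delirium among those excluded, true rates of 15% and 30% (or 20% in both groups), and a particular split between the groups. None of these comes from the documents. The point rests on the wording of the rule, not on those figures.

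**What to change.** Replace the single rule in the Study design section with two analysis sets:

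1. **Delirium set:** every operated patient with at least one postoperative 3DCAM, 4AT or CAM-ICU assessment, in ward or ICU.
2. **Complication set:** every operated patient, with events taken from the records and no ward-night or screening condition.

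Report by group how many patients died before any assessment and how many were not assessed for other reasons, so that readers can judge the remaining selection. Drop or reword the sentence claiming representativeness.

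The cost is small: a wording change and some record review, since the article already provides for ICU, record-based and CAM-ICU data. No further patients or visits are needed. One limit should be stated openly. Part of the data comes retrospectively from an ongoing delirium study, and for that part the wider sets can go only as far as the records which that study kept.

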### Documentation

The data is initially recorded and documented on paper and in an electronic database. This process is conducted by the doctors responsible for the study. The data is backed up and stored on a server located in Germany.

### Data monitoring

This study implements a monitoring concept to ensure data quality and safety in accordance with the guidelines for good clinical practice (GCP). Regular training of all personnel involved in the study, regular reviews for missing or inaccurate data and regular team meetings are conducted. The training, monitoring and meetings are intended to ensure a high level of protocol compliance and data quality as well as patient safety and rights.

### Risk-benefit assessment

This study is designed as a non-interventional observational study. No adverse effects on the participants are anticipated. Potential adverse events will be carefully monitored both intraoperatively and postoperatively, providing the opportunity to initiate appropriate interventions in a timely manner. Postoperative safety is enhanced through additional visits by the study team, which consists of study physicians and doctoral students. Regarding to data protection, the collection and storage of data is pseudonymized.

### Termination criteria

Consent to participate in the study may be withdrawn at any time, without providing reasons and without negative impact on further medical treatment. In the event of withdrawal from the study, all personal data already collected will be deleted immediately and completely.

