#### Primary outcome measures.

The primary aim is to determine the incidence of postoperative delirium on one of the first five days after surgery in the case group compared to the control group. The endpoint will be considered met if postoperative delirium is detected with at least one of the applied assessment methods used.

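### The deletion rule is not limited to revoked consent, so read literally it erases delirium already recorded in a patient withdrawn for a protocol violation

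*Protocol article*

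**What the plan says.** Termination criteria has two sentences. The first concerns the patient's right: "Consent to participate in the study may be withdrawn at any time, without providing reasons and without negative impact on further medical treatment". The second sets the consequence for the data: "In the event of withdrawal from the study, all personal data already collected will be deleted immediately and completely". It is worded for withdrawal in general, not for revoked consent.

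Study design, in the text after Table 2, lists the routes to withdrawal: "Withdrawal from the study happens may occur after the patient revokes consent, the planned operation is canceled, or if the study protocol is violated". The same section admits to the analysis patients with at least one night on a surgical ward and at least one postoperative screening, and adds: "Patients who do not complete these criteria are excluded from the statistical analysis". Deletion is not mentioned there.

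The primary outcome is the "incidence of postoperative delirium on one of the first five days after surgery in the case group compared to the control group", and "The endpoint will be considered met if postoperative delirium is detected with at least one of the applied assessment methods used". One positive screen is therefore enough. Risk-benefit assessment says that "the collection and storage of data is pseudonymized". Study design tolerates a dropout of 10% of recruited patients and foresees further recruitment above that.

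**The concern.** One term carries two scopes. In Study design it covers revoked consent, a cancelled operation and a protocol violation. In Termination criteria it triggers irreversible deletion with no restriction by cause. Anyone following the text literally would delete the record of a patient withdrawn for a protocol violation on, say, day 3, although a positive screen on day 1 or 2 had already met the endpoint.

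This is worse than exclusion from an analysis set. An excluded patient can be brought back in a sensitivity analysis; a deleted one cannot. If withdrawal is more likely in patients with delirium or a complicated course, which is plausible in a study with repeated cognitive testing, the deleted records contain a disproportionate share of events. Observed incidence then falls. The comparison between infection groups may shift in either direction, depending on how the withdrawal pattern differs between them.

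**Working it through.** **1. How the rules combine.** Take a patient who spends a night on the ward and screens positive on day 1.
- Study design: the criteria for the analysis are met.
- Primary outcome measures: the endpoint is met.
- Study design: a later protocol violation may lead to withdrawal.
- Termination criteria, read literally: the data are deleted.

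The first two rules count the event and the last removes it. A cancelled operation creates no such conflict, because there is no postoperative outcome to lose.

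**2. The plan's own figures** (Number of participants). 121 per group gives 242, and 242 × 1.10 = 266.2, stated as 266, or 133 per group. At exactly 10% loss, 266 × 0.90 = 239.4 remain. The required 242 are kept if at most 266 − 242 = 24 are lost (24/266 = 9.0%). Sample size is therefore hardly affected; the issue is selective loss.

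**3. Illustration of selective loss.** The article gives no delirium or withdrawal rates, so all of these are assumptions:
- true delirium p = 20% in the infected group and 10% in the control group, 133 per group;
- withdrawal with deletion in w_n = 5% of patients without delirium;
- withdrawal with deletion, after the positive screen, in a share w_d of patients with delirium.

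Observed rate = p(1 − w_d) / [p(1 − w_d) + (1 − p)(1 − w_n)]

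Patients lost per group = 133 × [p·w_d + (1 − p)·w_n]

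| w_d infected / control | Observed infected | Observed control | Difference (true 10) | Patients lost |
|---|---|---|---|---|
| 20% / 20% | 0.16/0.92 = 17.4% | 0.08/0.935 = 8.6% | 8.8 points | 10.6 + 8.6 = 19.3 |
| 30% / 10% | 0.14/0.90 = 15.6% | 0.09/0.945 = 9.5% | 6.0 points | 13.3 + 7.3 = 20.6 |
| 10% / 30% | 0.18/0.94 = 19.1% | 0.07/0.925 = 7.6% | 11.6 points | 8.0 + 10.0 = 18.0 |

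In the first row, 133 × 0.20 × 0.20 = 5.3 and 133 × 0.10 × 0.20 = 2.7 delirium cases are erased, about 8 in total.

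**4. Odds ratio.** The true value is (0.20/0.80)/(0.10/0.90) = 2.25. It is multiplied by the ratio of (1 − w_d)/(1 − w_n) in the infected group to that in the control group. It stays at 2.25 in the first row, becomes 2.25 × 0.7/0.9 = 1.75 in the second, and 2.25 × 0.9/0.7 = 2.89 in the third.

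**5. Against the tolerance.** 10% of 266 is 26.6. All three scenarios lose fewer (18 to 21), so the dropout threshold would not be reached.

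**The case against.** The strongest reply is that the deletion sentence directly follows one about the patient's consent, so it is naturally read as covering revoked consent only. Study design never mentions deletion. This stands as a likely intention, but the sentence does not say it, and it uses the broader term. That is why the point is one of reconciling two sections.

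Several stronger conclusions might be inferred, and the documents do not support them:
- **That every withdrawal, including those decided by the study team, is certain to lead to deletion.** This follows only from joining two sections, and the article does not say who decides that a violation warrants withdrawal.
- **That a patient who screens positive and then refuses a later test is deleted.** Nothing equates a refused test with withdrawal. Requiring only one postoperative screening points the other way: incomplete follow-up is accepted.
- **That the loss could never be examined by group.** Patient-level comparison would be impossible after full deletion, but an anonymous tally is not forbidden. Enforcing the 10% threshold presupposes at least a total count. Personal data is not defined, and whether the pseudonymized outcome record falls under it is left open.
- **That deletion after revoked consent is an error.** It is a legitimate commitment to participants' rights in an ethics-approved study.

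The magnitude is also open to challenge. All rates are assumed, and with equal withdrawal rates in the two groups the odds ratio does not move. The distortion of relative effect needs different withdrawal patterns by group, for which the article offers no evidence either way.

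**Conclusion.** The point holds as a conflict of wording with a statistical consequence. The deletion rule is not restricted by cause, the same term covers protocol violations elsewhere, and literal application would irreversibly remove primary events that the plan otherwise counts. Whether this will happen, and how often, cannot be known from the article.

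Under the assumed rates, a true difference of 10 points reads as 6.0 to 11.6. These figures treat all withdrawals in the scenarios as leading to deletion and as occurring after the positive screen. They bound an illustration and do not predict a bias. Incidence is biased downward only if patients with delirium withdraw more often than the others. No planned sample-size figure changes.

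**What to change.** Reconcile Termination criteria with the withdrawal list in Study design:
1. State that deletion applies only when the patient revokes consent to the use of the data, that is, asks for erasure.
2. For protocol violations, and for patients who only stop further visits, keep and analyse the data collected up to that point. Count an earlier positive screen as the endpoint met.
3. Report withdrawals as anonymous counts by infection group and reason.

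The cost is one paragraph in the protocol, matching consent wording, and an ethics committee notification, with no extra visits or staff. The reach is limited. Patients who consented under the existing wording remain under it, and recruitment was expected to end on 31.12.2024, so a consent change may affect few patients. Clarifying the scope and counting withdrawals stay useful. Losses from genuine requests for erasure will remain, and rightly so; the counts at least show how many there were in each group.

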### Statistical analyses

Participants will be divided into two cohorts at the start of the study, depending on previous SARS-CoV-2 infection. The case group consists of patients over 60 years of age undergoing elective surgery under general anesthesia lasting more than one hour and a previous SARS-CoV-2 infection. The control group consists of patients with the same characteristics but without a history of SARS-CoV-2 infection. Both groups include the same number of patients.

The results are analyzed by comparing the case group with the control group using appropriate statistical methods. When analysing the data, we will use statistical methods to take confounders into account.

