### Consent

Information regarding the study is provided both verbally and in writing during the preoperative anesthesia informed consent discussion. In this context, potential study participants are presented with an information sheet that explains the objectives, procedure, potential risks and benefits of the study in detail. Patients receive a copy of the information sheet for their personal use.

A detailed Covid history is also recorded. This includes the number and time of Covid infections, as well as the time between the last infection and the operation. In addition, postoperative pain, including pain therapy and postoperative nausea and vomiting are determined.

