In addition, a detailed history of smoking, chronic pain and COVID-specific medical history is obtained. Patients are interviewed about details of a SARS-CoV-2 infections and the dates of these infections. If the exact date of the last positive PCR test is unknown, participants are categorized into specific time intervals: less than 7 weeks, less than 3 months, less than 6 months, less than 1 year or more than 1 year. The COVID-related medical history also includes questions about the symptoms and their severity that occurred in the course of the COVID-19 disease. All presurgical data are summarized in Table 1.

**Table 1 pone.0323599.t001:** Presurgical data.

Presurgical data	Items
Demographic data	age, gender, height, weight, BMI
Risk classification	Clinical Frailty Scale, frailty criteria according to Fried, ASA, functional status, PONV risk
Risk factors	smoking history, alcohol consumption, chronic pain
Diseases	diagnosis, previous illnesses
Long-term medication	anticholinergics, benzodiazepines, tricyclic antidepressants, SSRIs, hypnotics, opioids, other, number of medications
COVID-specific medical history	previous SARS-CoV-2 infection, time of last SARS-CoV-2 infection, symptoms, severity of symptoms, complications, symptoms still present, long-COVID or post-COVID, SARS-CoV-2 vaccination status, time of last vaccination
Routine laboratory parameters	C-reactive protein, haemoglobin, creatinine, interleukin 6, urea, glucose, sodium, potassium
Surgical discipline	Orthopedics, Trauma surgery, Gynecology & Obstetrics, Upper GI tract, Lower GI tract, Hepato-biliary, Endocrine surgery and pancreas, Head and neck, Breast surgery, Cardiac, Thoracic (esophagus), Thoracic (lung and other), Vascular, Urology and kidney, Plastic/ dermatologic surgery, Other
Cognitive impairment	MOCA-Test, Mini Cog-Test

The four primary symptoms of COVID-19 disease are specifically recorded. These are cough, fever, runny nose and disturbance of the sense of smell and/or taste [10]. In addition, information about possible complications of the COVID disease, currently still existing symptoms, the possible presence of a long-COVID or post-COVID syndrome, vaccination status and past hospitalization are collected. Supporting S1 Fig presents the SPIRIT schedule of the study.

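### In the prospective part, infection group is known before delirium is rated and nothing keeps it from the raters, so differential detection of the primary endpoint is possible

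*Protocol article*

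**What the plan says.** **When the group is known.** The Statistical analyses section states: "Participants will be divided into two cohorts at the start of the study, depending on previous SARS-CoV-2 infection". The Consent section, describing the preoperative discussion, says "A detailed Covid history is also recorded". The Study design section adds "Patients are interviewed about details of a SARS-CoV-2 infections and the dates of these infections" and lists the COVID history in Table 1 with the presurgical data. The division into two cohorts follows in that section.

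**Who rates delirium.** According to Study design, "The occurrence of postoperative delirium is assessed during daily rounds by trained staff in the first five days after the operation", using the 3DCAM and the 4AT. The CAM-ICU "is routinely used by medical staff in the intensive care unit". The same section says that every participant is visited on all five days, without saying by whom. The Risk-benefit assessment mentions "additional visits by the study team, which consists of study physicians and doctoral students".

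**Who records the data.** The Documentation section says "This process is conducted by the doctors responsible for the study" and makes no distinction between exposure and outcome data.

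**What counts as an event.** Under Primary outcome measures, delirium detected by at least one of the methods on one of the five days meets the endpoint.

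**What is listed as a source of error.** The Discussion names recall bias, undetected infections, a learning effect, heterogeneity of the population, and the effect of education on the MOCA. Rater knowledge of infection group is not on the list.

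**The concern.** An exposure comparison is protected against outcome error only if the error is the same in both groups. Here the exposure is on file before the outcome is rated, and the rating is done by people at the bedside. A rater who knows that a patient had COVID-19, or still has symptoms of it, may resolve a borderline observation differently. The article's Background describes confusion and delirium as possible effects of the virus, so an expectation could exist even though the stated aim is neutral.

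The endpoint rule makes this matter more. One positive result among several methods and up to five days is enough, so a single doubtful call turns a non-event into a primary event.

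The Statistical analyses section promises to account for confounders. That deals with differences in baseline risk. It does not correct an outcome that was measured differently in the two groups.

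**Working it through.** **The plan's own figure.** The only figure that can be recomputed from its stated inputs is the final sample size: 242 × 1.10 = 266.2, given as 266. It reproduces, and this point does not depend on it. The 121 per group cannot be checked, because the delirium rates, significance level and power are not stated.

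**Is there a safeguard anywhere?**
- Study design describes raters, tools and days, but not what the raters know.
- Data monitoring offers training, checks for missing or inaccurate data, and meetings.
- Risk-benefit assessment mentions pseudonymisation, but as data protection. A rater at the bedside still knows who the patient is.
- Documentation does not separate the COVID history from the outcome record.

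None of these keeps infection group from a rater.

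**How large could the effect be?** The documents give no delirium rate, sensitivity or specificity, so every input below except the 121 per group is an assumption. There is no true effect in any scenario.

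Observed incidence = p × Se + (1 − p) × FP, where p is the true incidence, Se the sensitivity and FP the false-positive rate, all per patient over the five days.

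Take p = 0.15 in both groups and Se = 0.90, so p × Se = 0.135.

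| FP | Observed incidence |
|---|---|
| 5% | 0.135 + 0.85 × 0.05 = 0.1775 |
| 10% | 0.135 + 0.85 × 0.10 = 0.2200 |
| 3% | 0.135 + 0.85 × 0.03 = 0.1605 |
| 6% | 0.135 + 0.85 × 0.06 = 0.1860 |

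- FP 10% in infected, 5% in controls: risk ratio 0.2200 / 0.1775 = 1.24.
- FP 6% in infected, 3% in controls: risk ratio 0.1860 / 0.1605 = 1.16.
- With the first lean reversed (10% in controls): 0.1775 / 0.2200 = 0.81.

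**Chance of a false significant result** (121 per group, assumed two-sided 5% test, normal approximation):
- First case: standard error = √[(0.22 × 0.78 + 0.1775 × 0.8225) / 121] = 0.0512. The difference of 0.0425 is 0.83 standard errors, and the rejection probability is about 13%.
- Second case: standard error = √[(0.186 × 0.814 + 0.1605 × 0.8395) / 121] = 0.0486. The difference of 0.0255 is 0.52 standard errors, and the rejection probability is about 8%.

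**Range over other assumptions** (true incidence 10% to 30%, 121 per group, same test):

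| Se/Sp infected | Se/Sp controls | Spurious odds ratio | Rejection probability |
|---|---|---|---|
| 90/95 | 90/95 | 1.00 | 5% |
| 90/92 | 90/95 | 1.10 to 1.24 | 6% to 9% |
| 95/90 | 85/95 | 1.35 to 1.52 | 19% to 22% |
| 95/85 | 85/95 | 1.57 to 2.00 | 38% to 53% |

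Sp is the specificity, 1 − FP. The last two rows show what larger differences in detection would do. Nothing in the documents makes any row more likely than another.

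**The case against.** **The article is condensed.** Rotas and access to forms could stand in the full protocol, and no sentence says that raters know the group. This is fair as far as it goes. But the article does describe raters, tools, days and recorders, and it sets out its own list of error sources without this one. What a rater may know is also a matter of conduct, which an analysis plan cannot repair afterwards.

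**A reader might infer that the people who take the COVID history also rate delirium.** The documents do not say so. Study design speaks of trained staff on daily rounds. The Risk-benefit assessment says "Postoperative safety is enhanced through additional visits by the study team, which consists of study physicians and doctoral students", which is about safety and says neither that these visits are daily nor that they produce the ratings. Overlap is likely but remains an inference. The point does not need it, since a different rater is not kept from the group either.

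**A reader might infer that the result will be biased towards harm from infection.** The Outcomes section states a non-directional aim, and the direction of any lean is unknown.

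**The tools limit judgement.** All three are described as validated and reliable. The article's expansion of the 4AT includes attention and an abbreviated mental test, which depend on patient performance, as well as alertness and acute change, which rely more on the observer. This reduces the room for bias but does not close it.

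**Part of the data may be unaffected.** The CAM-ICU is applied by intensive care staff as routine, and they may not know the group. Patients from the earlier delirium study may have been rated before anyone classified their infection status. Their share is not given. Both objections stand, and they confine the point to the prospective part and mainly to the 3DCAM and 4AT.

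**Conclusion.** The point holds in limited form. As written, the prospective part allows raters to know infection group when they rate the primary endpoint, and nothing in the article prevents it or acknowledges it. Differential detection is therefore possible, and the any-method, any-day rule increases exposure to it.

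Its direction and size cannot be derived from the documents. A spurious risk ratio of about 1.24, with a false significant result in about 13% of such studies, rests on four assumptions: true incidence 15% in both groups, sensitivity 90%, false-positive rates of 10% versus 5%, and a two-sided 5% test at 121 per group. With 6% versus 3% the figures are 1.16 and about 8%.

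The documents do not support saying that raters were in fact influenced, or that patients from the earlier delirium study were rated with knowledge of their group. This should be corrected or declared, but it does not invalidate the study.

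**What to change.** **For assessments still to come**
- State in Study design that 3DCAM and 4AT raters are not given infection status.
- Keep the COVID history and group on a form or database page that raters do not open until the day 5 assessment is complete.
- Where the existing team allows, have someone other than the history-taker rate that patient.
- Record at each assessment whether the rater knew the status. Repeat the primary comparison using only assessments made unaware of group, and report how many such assessments each group contributes, because fewer assessments mean fewer chances of a positive result.

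**For patients already assessed**, including those from the earlier delirium study: report whether raters knew the infection status, and add possible detection bias to the error sources in the Discussion. Recruitment began on 06.09.2023 with an expected end of 31.12.2024, so this may be the only part still open. If raters were in fact kept unaware, one sentence in Study design settles the matter.

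**Cost.** A split form or access rule, one extra field per assessment, one sensitivity analysis, and minor scheduling effort. Team size is not given, so separating history-taker from rater may not always be feasible. Patients will occasionally reveal their status, which the awareness field would capture.
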